### **5.5 Methods in analysis to handle protocol non-adherence and any statistical methods to handle missing data**

Expert researchers will visually inspect all the scans and exclude any that cannot be analyzed due to data acquisition errors or artifacts. FMRI scans with critical motion will also be excluded. In our mixed effects models, we will include all available data for each timepoint.

## **6. Data monitoring committee, its role and reporting structure**

The PI, data manager, and study statistician will prepare a specific report for the Data Safety Monitoring Committee in advance of each bi-annual meeting. Specific attention will be given to data quality and timeliness, participant recruitment, accrual and retention, participant risk versus benefit, adverse events,

and other factors that can affect study outcome, including scientific developments that may have an impact on the safety of the participants or the ethics of the study. The procedures in place for monitoring adverse events as well as for site, data and statistical management will enable us to generate a timely report to the DSMB.

After each DSMB meeting, the DSMB will issue a report that summarizes:

- 1) All serious and unexpected adverse events (for example, inpatient hospitalizations) or other unanticipated problems that involve risk to study participants or others at either site, and whether these appeared related to the research assessment protocols. Reports will not specifically disclose the session/dose arm of the study unless this is required for safety reasons;
- 2) The committee's judgments as to whether participants' safety, privacy, and confidentiality has been consistently assured by the investigators;
- 3) Whether the DSMB recommends an interim analysis pertinent to evaluating participants' safety;
- 4) Judgments as to whether research instruments have been administered in a uniform manner and in a way that maintains participants' confidentiality;
- 5) The committee's review of the study's progress toward recruitment goals, quality of data (e.g., appropriate completion of forms), medication and psychosocial treatment adherence, and participant retention/attrition rates;
- 6) Its review of new scientific literature pertinent to the safety of participants or the ethics of research participation (for example, new therapeutic developments).

There will be regular, ongoing communication between the PI, the IRB, and the DSMB. IRB protocols and informed consent documents will be annually reviewed by the IRB; they will also be annually reviewed by the DSMB. The PI will take responsibility for reporting any serious adverse event (SAE) to their local IRB within 24 hours according to standard regulations. A SAE is defined as follows: death, life-threatening adverse event, inpatient hospitalization, persistent or significant disability/incapacity, and medically significant event. The PI will also be responsible for reporting any SAEs to the DSMB, and the NIDA Project Officer. Actions taken by the IRB in response to adverse event reports will be reported to the DSMB and the NIDA Project Officer and OHRP office.

## **7. Adverse event monitoring, reporting, and follow-up**

### **7.1 Adverse event reporting and harms**

An Adverse Event (AE) is defined as any medical occurrence in a participant, including any abnormal sign (e.g., abnormal physical exam or laboratory finding), symptom, or disease, temporally associated with the participant's involvement in the research, whether or not considered related to participation in the research. This definition includes concurrent illnesses or injuries and exacerbation of pre-existing conditions. The research team will collect AEs during study visits from Enrollment through Study

Termination. Participants will be asked directly how they are feeling during each contact, and AEs may be captured spontaneously during drug administration sessions, telephone calls, or other correspondence. Completed measures may create suspicion that an AE occurred; in this case, the site staff should follow-up with the participant. All AEs will be monitored by the study team until resolution or, if the AE becomes chronic, a cause can be identified.

Adverse events will be monitored for each participant at the time of enrollment and reported to the Stanford IRB at the continuing review, yearly. Unexpected deaths or life-threatening experiences related to the research must be reported to the Stanford IRB within 5 working days from the PD learning of the event.

Events and information which require prompt reporting the Stanford IRB

1. Unanticipated problems (UPs) involving risks to participants or others

Events (internal or external, deaths, life-threatening experiences, injuries, or other) occurring during the research study, which in the opinion of the Monitoring Entity or the PD meet all of the following criteria:

- Unexpected  
in terms of nature, severity, or frequency, given (a) the research procedures described in the protocol-related documents, and (b) the characteristics of the subject population being studied;

AND

- Related to participation in the research or there is a reasonable possibility or likelihood that the incident, experience, or outcome may have been caused by the procedures involved in the research;

AND

- Harmful  
the research places subjects or others at a greater risk of harm (including physical, psychological, economic, or social harm) than was previously known or recognized.

2. New Information that indicates a change to the risks or potential benefits of the research in terms of severity or frequency or impacts the subject's willingness to participate (e.g., DSMB/DSMC Report, other safety information or publication, suspension or premature termination by the sponsor or investigator).

3. Noncompliance: An action or activity in human subject research at variance with the approved IRB protocol, other requirements and determinations of the IRB, the HRPP Policy Manual and other applicable policies of Stanford University, SHC, LPCH, VAPAHCS (e.g., VHA Handbook 1200.5), Palo Alto Veterans Institute for Research (PAVIR) or relevant state or federal laws.

- a. When the event is:
  - i. Possibly serious

- Noncompliance that affects the rights or welfare of human subject research participants.
- ii. Possibly continuous
  - A pattern of noncompliance that continues to occur after a report of noncompliance and a corrective action plan has been reviewed and approved by the IRB, after an investigator has been warned to correct errors or noncompliance, or a circumstance in which an investigator fails to cooperate with investigating or correcting non-compliance.
- 4. Complaint unresolved by the research team.
- 5. Incarceration when in the opinion of the PD it is in the best interest of the participant to remain in the study.

If an AE is unresolved when a participant terminates from the study, a clinical assessment will be made by the site clinician and/or investigator as to whether continued follow-up of the AE is warranted. The severity of events reported on the “Adverse Events” will be determined by the site clinician as:

- Mild: No limitation in normal daily activity
- Moderate: Some limitation in normal daily activity
- Severe: Unable to perform normal daily activity

The relationship of each AE to the drug administration will be determined via analysis and the opinion of the investigator will be recorded at the time the event was recorded. Adverse events will be recorded for the duration of a participant’s active enrollment in the study and reported to the Stanford IRB upon continuing review, once a year.

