## **2. Methods**

### **2.1 Trial design and overview**

A mechanistic clinical MDMA trial to investigate the effects of MDMA on human brain circuit function using a double-blinded, within-subjects, placebo-and-baseline-controlled randomized design. The design includes four testing sessions including baseline, placebo, 80mg MDMA hydrochloride (HCl), and 120mg MDMA HCl, randomized within subjects.

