## **2.5 Interventions**

### *2.5.1 Intervention description*

After baseline visit, each participant will receive placebo, 80mg MDMA HCl, and 120mg MDMA HCl in a randomized order. Given the within-subjects design of the study, each participant will receive all three of the specified doses across the duration of the trial. Drug visits will be scheduled 10-14 days apart to avoid drug carry-over effects. Participants will arrive fasted for drug visits in the morning to reduce the risk of emesis. They will complete a urine drug screen and pregnancy test (if applicable) and have their baseline vitals recorded at the Stanford Center for Cognitive and Neurobiological Imaging, where they will be met by the study clinician. Participants will be instructed to orally ingest pills with water or an electrolyte solution. For safety reasons, pulse, blood pressure, temperature, and oxygen saturation will be monitored and recorded every 30 minutes throughout the drug visit. The total visit time for drug visits will be 6-8 hours.

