## **2.10 Recruitment and Study Cohort**

Healthy volunteers who report  $\geq 2$  uses of MDMA when they were 18 years or older, recruited to attain 4 sessions of data during functional brain imaging. A total of 40 participants will be recruited, equal

numbers of males and females will be recruited. Participants will be recruited through Facebook Ads using IRB-approved material. Individuals who express interest in the study will be directed to an online screening survey in REDCap. Completed screening surveys will be reviewed by research coordinators trained on the study protocol. Surveys will collect information about demographics, psychiatric diagnoses, substance use, and MRI compatibility. Individuals that are eligible by the criteria included in the screening survey will be contacted by a research coordinator to schedule a phone call. On this phone call, research coordinators will give the individuals additional information about the study and collect additional demographic information. Eligible individuals at this point will be consented by a research coordinator and will schedule an in-person screening visit at a research clinic to fully determine eligibility. The following procedures and assessments will be performed at the screening visit: ECG, physical examination, blood draw, vital signs, weight, urine drug test, pregnancy test (if applicable), Hamilton Anxiety Rating Scale (HAM-A), Hamilton Depression Rating Scale (HAM-D), the Mini International Neuropsychiatric Interview (MINI).

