#### *2.11.6 Plans to promote participant retention and complete follow-up*

To promote participant retention, participants agree to attend all four subsequent study visits at the time of the in-person screening visit. Follow-up measures will be completed via online survey at 1-week and 1-month, which research coordinators will review for completeness and follow up with participants by email as necessary. Participants who either elect to discontinue study procedures or are unable to continue study procedures will complete an abbreviated version of the study protocol according to the participant's desired level of participation and the safe level of participation as determined by the study clinician.

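### No general adverse event enquiry is specified after the third dose, so delayed events are solicited unevenly by visit position

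*Protocol*

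**What the plan says.** - **Where adverse events are collected.** Protocol section 7.1: "The research team will collect AEs during study visits from Enrollment through Study" Termination. The next sentence gives the method: "Participants will be asked directly how they are feeling during each contact, and AEs may be captured spontaneously during drug administration sessions, telephone calls, or"; the list of sources closes with correspondence of any further kind. Section 7.1 also tells staff to follow up when a completed measure makes them suspect an event, and later states that events are recorded throughout active enrollment.
- **How many visits there are.** Section 2.1: "The design includes four testing sessions including baseline, placebo, 80mg MDMA hydrochloride (HCl), and 120mg MDMA HCl, randomized within subjects". Section 2.11.6 likewise counts four visits after screening. The third drug visit is therefore the last.
- **Spacing.** Section 2.5.1: "Drug visits will be scheduled 10-14 days apart to avoid drug carry-over effects".
- **What follows the last visit.** Section 2.11.6: "Follow-up measures will be completed via online survey at 1-week and 1-month". Coordinators check these surveys for completeness and email participants where needed. Section 2.11.3.3 lists the instruments as DARS, DASS-21 and PCL-C. Its heading also names a 24-hour time point, which does not appear in section 2.11.1 or 2.11.6.

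**The concern.** A participant who develops a symptom some days after dose 1 or dose 2 returns to the site 10-14 days after that dose and is asked in person how they feel. A participant who develops the same symptom after dose 3 has no further visit. What is scheduled for that participant is a set of online scales on anhedonia, mood, anxiety, stress and trauma symptoms. A physical complaint has no evident place in them, although section 7.1 defines an adverse event as any medical occurrence, including abnormal signs and symptoms of any kind.

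Whether a delayed event is solicited thus depends on the position of the dose in the sequence. The count of delayed events could be too low. That count feeds the reports to the Data Safety Monitoring Board (section 6) and the assessment of relationship to drug, which section 7.1 says will be made by analysis and investigator opinion. An event that nobody asked about cannot be recovered at the analysis stage.

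**Working it through.** The protocol states no adverse event rate and no capture rate, so there is no figure of its own to reproduce. The check is a reading of the schedule followed by a bound.

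**Schedule, by dose position**

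| Dose position | Next in-person visit | Other scheduled follow-up described | General adverse event question specified |
|---|---|---|---|
| 1 | 10-14 days later (drug visit 2) | Online scales; the visit they are timed from is not stated | Yes, asked how they feel at the visit |
| 2 | 10-14 days later (drug visit 3) | As above | Yes, as above |
| 3 | None | Online DARS, DASS-21, PCL-C at 1 week and 1 month | None described |

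**Inputs**

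- Participants: 40 (section 2.10, "A total of 40 participants will be recruited, equal" numbers by sex).
- Doses per participant: 3 (section 2.5.1, "each participant will receive all three of the specified doses across the duration of the trial").
- Missed share *m* of delayed events after dose 3: not given, so varied from 0 to 1.

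**Share of doses affected**

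- All doses: 40 × 3 = 120. Third doses: 40. Share: 40/120 = 33.3%.
- Active doses: 40 × 2 = 80. Expected active third doses: 80/3 = 26.7, again 33.3%. The remaining third doses, 40 − 26.7 = 13.3 on average, are placebo.

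**Possible undercount**

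Assume that delayed events are equally likely after each dose position and that all are captured after doses 1 and 2. The pooled shortfall in delayed events is then *m*/3.

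| Share missed after dose 3 (*m*) | Pooled shortfall (*m*/3) |
|---|---|
| 0 | 0% |
| 0.25 | 8% |
| 0.50 | 17% |
| 0.75 | 25% |
| 1 | 33% |

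**Does it favor one dose?**

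Dose order is randomized, so each dose is expected third in 40/3 = 13.3 participants and the expected loss is the same for each. Section 2.6 states no balancing of positions. Assuming simple randomization, the number of participants with a given dose in third position has SD √(40 × 1/3 × 2/3) = 3.0 and lies between 8 and 19 with probability 0.96. The largest and smallest of the three counts differ by about 6 on average, and by 9 or more with probability 0.23.

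For illustration, take a split of 18 against 9, no capture after dose 3, and an assumed true delayed-event rate of 15% for both doses:

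- Dose third in 18 participants: 0.15 × (1 − 18/40) = 8.3%, or 3.3 expected events in 40.
- Dose third in 9 participants: 0.15 × (1 − 9/40) = 11.6%, or 4.65 expected events in 40.

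The gap is about 1.35 events, in a scenario chosen to be unfavorable.

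**The case against.** The strongest objection is that section 7.1 does more than collect at visits. It promises a direct question at every contact, accepts telephone calls and other correspondence as sources, has staff act on suspicious questionnaire answers, and keeps the recording window open throughout enrollment. A reader might infer from the visit schedule that delayed events after dose 3 are never asked about. The text does not support that: DASS-21 and PCL-C ask about psychological symptoms, and an online survey might be meant to count as a contact. Nor is absence from the list in section 2.11.3.3 strong evidence. That list is an inventory of self-report instruments, and no adverse event form is listed there for the drug visits either, although section 7.1 refers to one. Operational documents may hold more.

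A reader might also infer that rates are in fact undercounted or that doses are compared unfairly. Neither follows. The missed share is unknown and could be zero. Full capture after doses 1 and 2 is itself assumed, since the protocol promises a question about how participants feel, not a review of the whole interval. Any loss is equal across doses in expectation. Adverse event rates are not among the outcomes in section 4, and section 5 plans no comparison of them by dose.

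These points limit the size of the concern but do not remove it. The protocol does not say that a survey is a contact, and no staff member puts a question in one. Telephone calls and correspondence are named only as routes for spontaneous reports, and no call is scheduled after dose 3. Action on suspicious answers reaches only what the three scales measure. The recording window sets a period without saying how events are to be sought in it, and its end, Study Termination, is not defined.

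**Conclusion.** The concern holds as a gap in how delayed adverse events are solicited. After 40 of 120 planned doses (33%) the protocol specifies no general adverse event enquiry, whereas the other 80 are each followed by an in-person visit 10-14 days later. The possible loss is 0 to 33% of delayed events. The upper end requires that nothing is captured after dose 3, that everything is captured after doses 1 and 2, and that risk is the same after each position.

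The gap concerns mainly physical symptoms that begin after the participant has left the site. Events during the monitored drug visits are unaffected (section 2.5.1: "The total visit time for drug visits will be 6-8 hours"). No systematic bias between doses is expected; a chance imbalance in third positions could produce a small apparent difference. The point merits action because the remedy is cheap and later analysis cannot replace data that were not collected.

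**What to change.** 1. Add one general adverse event question to the existing online follow-up surveys, including those after the third dose: any new symptom since the last drug visit, with its onset date. Have staff contact every participant who answers yes.
2. State in section 7.1 that adverse event collection runs through the 1-month survey, define Study Termination to match, and say whether an online survey counts as a contact.
3. Reconcile sections 2.11.1, 2.11.3.3, 2.11.6 and 7.1 on the follow-up schedule. In particular, settle whether the 24-hour time point exists, and state which drug visits the follow-ups are timed from.

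The cost is one REDCap item, an IRB amendment and a few more adverse event entries to process.

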## **7.2 Follow-up report**

If an SAE has not resolved at the time of the initial report and new information arises that changes the investigator’s assessment of the event, a follow-up report including all relevant new or reassessed information (e.g., concomitant medication, medical history) should be submitted to the IRB. The investigator is responsible for ensuring that all SAE are followed until either resolved or stable.

## **8. Internal audit, protocol amendment, and study dissemination plans**

### **8.1 Frequency and plans for auditing trial conduct**

We have established an internal auditing process to ensure study compliance is followed. A nominated study monitor will conduct a bi-annual audit outlined in the clinical monitoring plan for this study. The study monitor will collect study essential files including but not limited to; IRB-approved study material, study visit documentation, study drug logs, NIH annual progress report, and DSMB Bi-Annual reports. Once reviewed, the study monitor will work with the study coordinator to ensure all items to be corrected are addressed and corrected. This monitoring plan will occur at study initiation, bi-annually during study execution, and at the end of the study.

## **8.2 Plans for communicating important protocol amendments to relevant parties (e.g., trial participants, ethical committees)**

Upon important protocol amendments this information will be communicated via email effectively to all necessary parties. These parties include but are not limited to the DSMB, the IRB, study staff, study participants, sponsors, and anyone else that necessitates this kind of information. If follow-up is required, study staff and the PI will employ a meeting to ensure clarity on the protocol amendment.

## **8.3 Dissemination plans**

The plan to disseminate results will be via publications in scientific journals available to the public. All participants will be on mailing lists and informed of when a paper is published.

